## Abstract

**Background:**

In Switzerland, skin cancer is one of the most common neoplasms. Melanoma is the most aggressive one and can be lethal if not detected and removed on time. Nonmelanoma skin cancer is more frequent as melanoma; it is seldom lethal but can disfigure patients in advanced stages. General practitioners (GPs) are often faced with suspicious skin lesions of their patients.

**Methods/Design:**

*Design: *Randomised controlled trial (RCT).

*Population: *60 GPs, randomised into intervention group and control group.

*Intervention: *GPs get a Lumio loupe, a digital camera and continuous feedback based on pictures of skin lesions they send to the Dermatologist.

*Primary outcome: *Competence in the diagnosis of skin cancer by GPs, measured as the percentage of correctly classified pictures of skin lesions.

*Measurements: *At baseline, and prior to any intervention (T_0_), GPs will be asked to rate 36 pictures of skin lesions according to their likelihood of malignancy on a visual analogue scale (VAS). After a full day training course with both groups (T_1_) and after one year of continuous feedback (T_2_) with the intervention group, we will repeat the picture scoring session with both groups, using new pictures.

**Discussion:**

We want to determine whether a multifaceted intervention (including technical equipment and a continuous feedback on skin lesions) leads to an improved competence in the diagnosis of skin cancer by GPs. This study addresses the hypothesis that an additional feedback loop, based on pictures performed in daily practice by GPs is superior to a simple educational intervention regarding diagnostic competence. We expect an improvement of the competence in skin cancer diagnosis by GPs in both groups after the full day training course. Beside this immediate effect, we also expect a long term effect in the intervention group because of the continuous problem based feedback.

**Trial registration:**

ISRCTN: ISRCTN29854485

## Background

Skin cancer is one of the most common neoplasms in Switzerland [1] and in Central Europe Switzerland is one of the countries with the highest prevalence of melanoma [2].

There are three main types of skin cancer: basal cell carcinoma (BCC), squamous cell carcinoma (SCC) and melanoma. Within skin cancers, melanoma is the most aggressive one and can be lethal if not detected and removed on time. It is responsible for more than 90% of all skin cancer related deaths. The lifetime risk for melanomas in Switzerland for newborns of the year 2000 is estimated to be 1:80 [3], there are currently approximately 1900 new cases of melanoma per year in Switzerland [1] and the rate of incidence continuously increases. Due to a lack of adequate therapies for metastatic melanoma, the best management option currently remains early diagnosis and prompt surgical excision of the primary cancer. If diagnosed and treated at early stages most melanoma can be cured.

BCC and SCC (summarized as nonmelanoma skin cancer, NMSC) are more frequent than melanoma; they are less dangerous because they rarely spread in the body. Due to their high incidence, their aggressive, destructive growth pattern and their tendency to recur after treatment, the morbidity and costs related to these cancers are very high [4].

Due to the rapidly rising incidence of skin cancer, GPs are more and more faced with suspicious skin lesions in their patients. Appropriate knowledge and continuous training about suspicious skin lesions are crucial to handle these lesions correctly. An important condition for an optimal patient care is the collaboration of GPs with Dermatologists in a multidisciplinary treatment team [5].

## Methods/Design

### Hypothesis

A multifaceted intervention including technical equipment and a continuous feedback (provided by a Dermatologist) leads to an improved competence in the diagnosis of skin cancer by GPs.

### Study design

This study is a (prospective) randomised, two-armed study; randomised and controlled at the GP level. The intervention includes a Lumio loupe (magnifying glass with integrated polarized light source allowing subsurface examination), a digital camera and continuous feedback on all pictures of skin lesions the GP sends to the Dermatologist.

### Primary outcome

Competence in the diagnosis of skin cancer by GPs, measured as the percentage of correctly classified pictures of skin lesions.

### Inclusion criteria for general practitioners

All GPs in the Canton of Zurich will be invited to join the study by postal letters and information sessions provided by members of the study centre. 60 GPs are projected to be part of the study. Any general practitioner who provides basic medical care with a workload of at least 20 hours per week, who does not plan to retire or to move away during the study period is entitled to participate in the study.

### Procedure of the study

The procedure of the study is summarised in Figure 1.

**Figure 1 F1:**
[figure not shown]
**Study design**.

#### Both groups

At baseline, and prior to any intervention (T_0_), the GPs will be asked to rate 36 pictures of skin lesions according to their likelihood of malignancy on a VAS. After a full day training course with both groups (T_1_) and after one year of continuous feedback (T_2_) with the intervention group, we will repeat the picture scoring session with both groups.

#### Intervention group

After the initial picture scoring sessions and the full day training course, every GP will receive a Lumio loupe (magnifying glass with integrated polarized light source allowing subsurface examination) and a digital camera. During his normal consultations, the GP takes pictures with the digital camera of those skin lesions he wants to get feedback on. The pictures are made anonymous and sent by e-mail to an address, specially created for this study. Alternatively, the memory cards with the pictures will be sent once per week to the study centre.

Based on those pictures, a continuous problem based feedback and teaching to the GPs will be conducted. As kind of reminder, every GP will receive a monthly update on the study, including the number of pictures he sent to the Dermatologist compared to the number of pictures sent by the other GPs in the intervention group.

We will not change the current health care practice for the patients; malignant suspicious lesions will be removed immediately. In case of an additional teledermatological diagnosis "malignant suspicious", the GP will be informed directly and has to contact the patient immediately to prevent a delay in excision and further treatment.

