### Time frame

The time frame of our study is shown in Figure 2. The study is intended to last around 16 months from which the intervention with the continuous feedback will last 12 months.

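### The weekly memory-card route puts a wait of up to 7 days before dispatch ahead of the dermatologist's reading that triggers the suspicious-lesion alert; a same-day e-mail rule for uncertain, untreated lesions would be a cheap, minor improvement

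*Protocol article*

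**What the plan says.** All of the relevant procedure is in the Intervention group section of the Protocol article.

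- **What is photographed.** During consultations, "the GP takes pictures with the digital camera of those skin lesions he wants to get feedback on". The choice is the GP's, and no level of suspicion is tied to a route.
- **First route.** "The pictures are made anonymous and sent by e-mail to an address, specially created for this study". No time limit for sending is given.
- **Second route.** "Alternatively, the memory cards with the pictures will be sent once per week to the study centre".
- **Care outside the study.** "We will not change the current health care practice for the patients; malignant suspicious lesions will be removed immediately".
- **Alert.** "In case of an additional teledermatological diagnosis" of suspected malignancy, "the GP will be informed directly and has to contact the patient immediately to prevent a delay in excision and further treatment".

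The Time frame section adds that "the intervention with the continuous feedback will last 12 months". The Background section says of metastatic melanoma that, for want of adequate therapies, "the best management option currently remains early diagnosis and prompt surgical excision of the primary cancer".

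**The concern.** The alert is there to avoid delay, but it can start only after the dermatologist has seen the picture. On the card route, pictures collect for up to a week before they leave the practice. The immediacy required of the GP therefore applies only after a batching step that the protocol itself has set.

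The lesions at stake are a narrow group: those that the GP has photographed but neither removed nor referred, and that the dermatologist would call suspicious. Lesions that the GP already suspects are removed at once and do not wait for the reading. For the narrow group, the alert reaches the patient some days later than it need do, although the study already has a mailbox that would avoid most of the wait. This is a matter of patient safety and logistics. It does not touch the trial's inference.

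**Working it through.** The article gives no figure for the delay, so there is no stated number to reproduce. The only numerical inputs are the once-per-week interval (Intervention group section) and the 12 months of feedback (Time frame section). Everything else below is a labelled assumption. All waits run from photograph to dispatch.

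**1. Card route, photographs spread evenly over seven days (assumption).** The wait W is uniform on 0 to 7 days.

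- Mean: 7/2 = 3.5 days; maximum 7 days.
- Share waiting more than 1 day: (7 − 1)/7 = 6/7 = 86%.
- Share waiting more than 3 days: (7 − 3)/7 = 4/7 = 57%.

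**2. Card route, photographs on Monday to Friday only, fixed dispatch day (assumption).** The waits are in whole days, for photographs taken on Monday, Tuesday, Wednesday, Thursday and Friday in turn.

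| Dispatch day | Waits | Mean | Maximum |
|---|---|---|---|
| Friday | 4, 3, 2, 1, 0 | 10/5 = 2.0 | 4 |
| Wednesday | 2, 1, 0, 6, 5 | 14/5 = 2.8 | 6 |
| Monday | 0, 6, 5, 4, 3 | 18/5 = 3.6 | 6 |

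The even-spread mean of 3.5 lies near the top of this range. Under either assumption the wait is a matter of days.

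**3. Same-day e-mail.** The wait is 0 to at most 1 day, with a mean between 0 and 0.5. Against the even-spread card route, the mean gain is 3.5 − 0.5 = 3.0 to 3.5 − 0 = 3.5 days. On the whole-day count of step 2, same-day e-mail counts as 0, so the mean gain is 2.0 to 3.6 days.

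**4. E-mail without a send-by rule.** If a GP e-mails every b days (assumption), the mean wait is b/2, and card minus e-mail is (7 − b)/2 under even spread.

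- b = 1: 3.0 days
- b = 2: 2.5 days
- b = 3: 2.0 days
- b = 7: 0 days

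The gain therefore comes from the same-day rule, not from e-mail as such.

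**5. What is not counted.** Postal and reading times are not stated. If the post took 0 to 3 days (assumption), the even-spread mean up to arrival would be 3.5 to 6.5 days and the maximum 7 to 10 days. Reading time would come on top for both routes.

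**6. Exposure.** A GP who uses cards for the full 12 months goes through about 365/7 = 52 weekly cycles. That is a count of cycles, not of affected patients. The share of GPs using cards and the share of lesions in the narrow group are not stated, so the number of patients cannot be computed.

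**The case against.** The strongest reply is that nothing here is contradictory. E-mail is named first and the card is an alternative. The immediacy applies to the GP's contact with the patient once a reading exists, and no time from photograph to reading is promised. Send-by times and triage are operating details that a condensed article may leave to the full protocol, and nothing stops a GP from e-mailing a worrying picture at once. This stands in part: the statements are compatible, and the missing e-mail deadline is not itself a finding. But the weekly interval is not an omission. It is a stated rule, and nothing in the article restricts which lesions it may cover.

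A second reply is that no patient is worse off. Current care is unchanged, suspected lesions are removed at once, and control practices get no teledermatological assessment until the study ends. This stands in full. A reader might infer that the card route delays treatment compared with usual care. The article does not support that, because usual care has no such reading. Nor does anything in the article show that a few days here changes a patient's outcome; the Background supports prompt excision only in general terms.

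A third reply is that the remedy misses the lesions most dependent on the reading, namely those that the GP confidently but wrongly thinks benign. They would still wait on the card. That is true, and it limits the benefit. The remedy mainly helps lesions about which the GP already has some doubt.

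**Conclusion.** The point holds as a cheap, minor improvement to an added safeguard. The protocol lets any photographed lesion go by a card sent once per week, which puts a wait before dispatch of up to 7 days ahead of the reading on which the alert depends. The mean depends on an assumption: 3.5 days with photographs spread evenly, or about 2.0 to 3.6 days with working-week photographs and a fixed dispatch day.

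Two stronger readings should be avoided. One might take these figures as the time to the alert, or take the one-day figure in the fix as the whole turnaround. Both cover the sending step only, because the article states neither postal nor reading time. One might also credit e-mail itself with the full gain. Without a send-by rule its mean advantage ranges from 0 to 3 days over the sending frequencies considered.

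The primary outcome, the sample size and the analysis are not affected.

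**What to change.** Add one or two sentences to the Intervention group section. Pictures of lesions that have not been excised or referred, and on which the GP is uncertain, go by e-mail to the existing study address on the day they are taken. The weekly card stays available for lesions already dealt with, lesions that the GP confidently judges benign, and back-up copies. The sending step for the uncertain, untreated lesions then takes at most 1 day.

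The cost is small because the mailbox already exists. GPs who prefer cards would have slightly more to do and might submit slightly fewer uncertain cases, which would slightly reduce the feedback they receive. Leaving confidently misjudged lesions on the card is the price of not barring that route.

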#### Control group

GPs in the control group also join the initial picture scoring sessions and the full day training course, but they will receive neither the technical equipment nor the continuous feedback until the end of the study. After the end of our measurements, GPs in the control group will also receive the Lumio loupe, the camera and the possibility to send pictures of skin lesions for teledermatological assessment.

### Sample Size

The power calculation was based on data from previous studies, as e.g. Gerbert et al. [6] who showed that the improvement in correct answers with an educational intervention could be about 13-36%. Due to the continuous feedback via teledermatology we assume this effect even to be greater.

Based on these assumptions, a power of 80% and a significance level of 5% (alpha error) the sample size has to be 53 GPs. With a drop out rate of 10% we concluded that 60 GPs would be necessary.

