### Training course

The GPs in both groups will receive a full day training course on skin cancer diagnosis which is going to be organized by [name] and his collaborators from the Department of Dermatology of the University Hospital Zurich. This training course will contain structured lectures and interactive problem based teaching.

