## Discussion

As shown in Figure 3 we expect an improvement of the competence in skin cancer diagnosis after the full day training course at T_1 _compared to T_0 _in both groups. This improvement will probably fade away in the control group after one year. It is known from different studies [8,9] that the effect of a continuing medical education (CME) is superior to the effect of single interventions. Therefore, we expect at T_2 _a significant difference in the competence in the diagnosis of skin cancer between the intervention group and the control group. We even expect that in the intervention group, GPs will score better at T_2 _than they did at T_1_, this would show the effect of the continuous problem based teaching.

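### The 80% power claim rests on the gain from an educational intervention, but both arms take the training course before randomisation, so it is unsupported for the randomised comparison

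*Protocol article*

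**What the plan says.** The Sample Size section of the protocol article rests on earlier studies in which "the improvement in correct answers with an educational intervention could be about 13-36" per cent. It then adds: "Due to the continuous feedback via teledermatology we assume this effect even to be greater". From there it goes straight to the result: with "a power of 80% and a significance level of 5% (alpha error) the sample size has to be 53 GPs", raised to 60 for 10% dropout. It names no between-arm difference, control-arm percentage, standard deviation or sidedness, and does not say whether the range is in absolute or relative terms.

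Three other sections fix what the arms share:

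- Training course: "The GPs in both groups will receive a full day training course on skin cancer diagnosis".
- Control group: "GPs in the control group also join the initial picture scoring sessions and the full day training course". These GPs get no equipment or feedback until the measurements are over.
- Randomisation and Blinding: the randomisation list is drawn up only after the initial scoring sessions and the course.

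The outcome is a score per GP, "measured as the percentage of correctly classified pictures of skin lesions", on 36 pictures per session. On the controls' course up to T2, the Discussion says "This improvement will probably fade away in the control group after one year". It also expects the intervention arm to do better at T2 than at T1. It puts no size on either expectation, and the Sample Size section refers to neither.

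**The concern.** A sample size calculation has to be driven by the difference expected between the randomised arms. The cited range is the gain from teaching. In this trial teaching is given to everyone before allocation, so its immediate gain is common to both arms and cancels from the comparison. What remains is the increment from equipment and feedback, together with any loss of the training gain among controls. Taking the education gain as the starting point and assuming more on top ties the 80% to a quantity that the trial does not compare.

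What is at stake is the reading of the result. If the arms do not differ significantly at T2, readers will judge this against a stated 80% power. If the true increment is modest, the actual power may be well below that, and the protocol gives them no means of knowing.

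**Working it through.** **Inputs from the protocol article.** Power 80%, alpha 5%, effect 13 to 36%, 53 GPs before dropout, 10% dropout, 60 GPs (all Sample Size); a percentage score per GP (Primary outcome).

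**Assumptions, not in the document.** Two-sided test, 1:1 allocation, the range read as percentage points, and an SD of GP scores of 10 to 15 points.

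**1. What the arms compare at T2.** Let g be the gain from the course at T1, a the further change in the intervention arm from T1 to T2, and f the loss in controls from T1 to T2. Relative to T0:

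- Intervention arm at T2: g + a
- Control arm at T2: g − f
- Difference: (g + a) − (g − f) = a + f

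The training gain g drops out. The sample size text supplies a range for an education gain, which corresponds to g. The protocol supplies no number for a or f.

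**2. The plan's own figures.**

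- Dropout: 53 / 0.9 = 58.9, so 60 is adequate.
- The 53 cannot be derived from the printed inputs alone, but unstated inputs do give it. For two means, 26.5 GPs per arm give 80% power (t-test) at a standardised difference of 0.785. A 13-point difference then implies an SD of 13 / 0.785 = 16.6 points.
- If instead each GP were a single yes/no outcome, which the protocol does not define, a 36-point difference from a control rate of 48 to 50% needs 26 per arm, 52 in total.

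So 53 is neither confirmed nor refuted.

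**3. Power for the cited effect, if it were the between-arm difference.** For a two-sample t-test on GP scores, 13 points, 26.5 per arm:

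| SD (assumed) | GPs needed for 80% | Power with 53 GPs |
|---|---|---|
| 10 | 22 | over 99% |
| 12 | 30 | 97% |
| 15 | 44 | 87% |

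**4. What the trial can detect.** Evaluable GPs: 60 × 0.9 = 54, or 27 per arm. The difference detectable with 80% power is d × SD, where d ≈ (1.96 + 0.84) × √(2/27) = 0.76 by the normal approximation and 0.777 by the t-test.

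- SD 10: 0.777 × 10 = 7.8 points
- SD 15: 0.777 × 15 = 11.7 points

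**5. A smaller increment.** Suppose g is 13 points, controls lose half of it (f = 6.5) and the intervention arm holds its level (a = 0). The difference is then 6.5 points. With 27 per arm:

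| SD (assumed) | Standardised difference | Power |
|---|---|---|
| 10 | 0.65 | 65% |
| 12 | 0.54 | 50% |
| 15 | 0.43 | 35% |

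This scenario is an illustration. The Discussion expects a to be above zero, and 6.5 + 6.5 would give the full 13 points.

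**The case against.** The best defence has four parts.

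- **A journal article condenses.** An SD or control percentage may well stand in the full protocol. This is right, and leaving them out is not the point here. The point is that the basis the article does state is the effect of something both arms receive.
- **The benchmark may be meant for the feedback.** Feedback on the GP's own pictures is itself teaching, so a study of education could serve as a yardstick for it. That is a possible reading, but an optimistic one. The section speaks of the cited effect becoming greater through feedback and never separates the shared gain from the increment.
- **The gap at T2 could be large.** The Discussion expects fading in controls and further improvement in the intervention arm. This stands. A reader might infer that the assumed effect needs the control gain to vanish almost completely, and that would be wrong: partial fading plus added gain can reach 13 points. Neither component is quantified or linked to the calculation.
- **On GP scores the trial is not small.** With an SD of 10 to 15 points, 53 GPs give 87% to over 99% power for 13 points. This also stands, and it limits how serious the point is.

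A reader might also take the Chi-square test named under Analysis to mean one yes/no result per GP, and conclude that far more GPs are needed for 13 points. The document does not support that: Primary outcome and Data collection define a percentage over 36 pictures, not a pass or fail per GP.

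**Conclusion.** The concern holds as a wrong stated basis for the power claim. The 80% is tied to a gain that both arms share, so it is unsupported for the comparison of loupe, camera and feedback added to training against training alone. This conclusion follows from the protocol's own sections and needs no assumed number.

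It does not follow that 53 GPs is wrong or that the trial is underpowered. A reader might infer either, but the printed inputs do not determine 53 and ordinary unstated inputs reproduce it. What can be said is conditional. With 54 evaluable GPs, 80% power is reached at 0.78 SD, or 7.8 to 11.7 points, which lies below the bottom of the cited range. At 6.5 points the power is about 65% to 35%. Both ranges rest on the assumed SD of 10 to 15 points, equal arms and a two-sided t-test on GP scores.

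The section should be corrected, but nothing here calls for a larger or different trial.

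**What to change.** Keep 60 GPs. In the Sample Size section, remove the statement that the effect exceeds the cited range as the basis for the calculation, and state the power for the incremental difference at T2 on GP-level percentage scores. For example:

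> *The comparison of interest is the difference between arms at T2 in the percentage of correctly classified pictures per GP, after training in both arms. With 54 evaluable GPs (27 per arm) and a two-sided 5% level, the trial has 80% power for a difference of 0.78 SD, that is 7.8 to 11.7 percentage points if the SD is 10 to 15 points (assumed). For a difference of 6.5 points the power would be about 65% to 35% over that range.*

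If the trial team has an SD from its own or earlier data, it should replace the assumed range and be named as the source. The cost is a few sentences in one section. Design, endpoint and recruitment target stay as they are. The claim becomes conditional on a stated difference, and it then concerns the comparison that the trial makes.
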